**Methods:**

A total of 4,000 adult participants meeting International Classification of Sleep Disorders, 3rd Edition (ICSD-3) criteria for insomnia disorder will be recruited from community or clinical settings. Eligible participants will be invited to complete the multi-dimensional assessments via a digital platform, including a structured interview, questionnaires, cognitive tasks, sleep-activity diary, physiological characteristics, and ecology momentary assessments, as well as 7-day physical activity and sleep tracking using wearable devices. All participants will be followed up at 6 and 12 months. The primary outcome is the identification of multi-modal subtypes of insomnia disorder and their correlates. Secondary outcomes include the longitudinal trajectories of these subtypes, associated risk factors, and mental health outcomes.

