### Study population

To determine the subtypes of insomnia disorder and explore their predictive value for trajectory and intervention outcomes, an estimated 40–80 variables will be included in the statistical model. Based on an estimated events per variable (EPV) of 50 to ensure sufficient statistical power, a total of 4,000 participants are required at the baseline [28].

Participants aged 18–65 years with a lifetime history or current insomnia disorder will be recruited. Subjects will be included in the study if they meet the following inclusion criteria: a. Previously or currently meeting the diagnostic criteria for insomnia disorder in ICSD-3; b. Ability to read and understand Chinese, and use the devices required for the study; c. Ability to provide informed consent. The exclusion criteria are: a. Lifetime history of schizophrenia, intellectual disability, or severe physical illness; b. Pregnancy or lactation; c. current involvement in other clinical research projects.

As of June 2025, 33 study sites specializing in psychiatry, neurology, or sleep medicine have taken part in the current study. The principal research centre of the DIMOSI study is located at the Guangdong Mental Health Centre, Guangdong Provincial People’s Hospital (Guangdong Academy of Medical Sciences), Southern Medical University, Guangzhou, China. Additionally, 33 study sites across various regions of China have joined as collaborative institutes (Fig. 2).

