#### Multimodal data integration

Questionnaire, EMA, wearable, and cognitive task data will be integrated using a unified preprocessing and clustering framework. Within each modality, features are selected to capture distinct aspects of insomnia-related functioning, such as mental disorders and symptoms, cognition, objective sleep parameters, and demographic characteristics. Variables with low variance or > 30% missingness will be excluded. To eliminate the influence of differing scales and units across features, continuous variables are standardized using Z-score normalization.

To address multicollinearity and redundant information, we construct a pairwise correlation matrix and visualized it with a heatmap to identify highly correlated feature pairs (|r| > 0.8). Two mainstream strategies will be considered: (1) Feature selection using Lasso regression with 10-fold cross-validation to retain the most informative variables while shrinking redundant coefficients to zero; and (2) Feature dimensionality reduction using principal component analysis (PCA), which transforms correlated variables into orthogonal principal components while preserving most of the data variance. After preliminary testing, PCA is selected as the final approach based on its superior performance in preserving global data structure and compatibility with K-means clustering’s independence assumptions. Components explaining > 85% of the cumulative variance will be retained for subsequent analyses.

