#### Subtyping procedures

The standardized features from each modality are concatenated into a single feature matrix, and variance normalization is applied to balance the contribution of different modalities in subsequent analyses [75, 76]. PCA was further applied for dimensionality reduction, followed by K-means clustering to identify distinct insomnia subtypes.

The optimal number of clusters (k) was determined using the elbow, silhouette, and Gap statistics. To assess clustering robustness, bootstrap resampling (1,000 iterations) and consensus clustering will be performed [77]. Cluster characteristics will be summarized using standardized centroid differences and key feature importance, providing interpretable profiles of each subtype. Sensitivity analyses will be conducted to compare equal-weight versus data-driven weighting schemes to evaluate the robustness of the clustering results. The defining features of each cluster are examined to understand the underlying pathophysiological mechanisms and clinical presentations.

Aggregated features obtained from Zhiyoumian and wearable devices as well as their changes from baseline, will be incorporated into the statistical analyses. Machine learning techniques will be applied to build predictive models evaluating the stability and clinical predictive value of these subtypes.

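### Of the three criteria for k only Gap can select a single cluster, and the robustness check tests whether a partition repeats, not whether subtypes exist

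*Protocol article*

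**What the plan says.** The abstract's Methods paragraph sets the aim: "The primary outcome is the identification of multi-modal subtypes of insomnia disorder and their correlates". Multimodal data integration gives the preparation: "continuous variables are standardized using Z-score normalization" and "Components explaining > 85% of the cumulative variance will be retained for subsequent analyses". Subtyping procedures then gives the method, "PCA was further applied for dimensionality reduction, followed by K-means clustering to identify distinct insomnia subtypes", and the rule for the number of clusters, "The optimal number of clusters (k) was determined using the elbow, silhouette, and Gap statistics". The robustness check is "To assess clustering robustness, bootstrap resampling (1,000 iterations) and consensus clustering will be performed". A sensitivity analysis compares two weighting schemes, and predictive models are to evaluate the subtypes' stability and clinical value. The article names no single-population reference for silhouette or stability, and no result that would count against distinct groups.

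**The concern.** K-means divides any data set into the number of pieces requested. Whether those pieces are subtypes has to come from the criteria applied to them. Two of the three criteria for k cannot favour one population, and the robustness check asks a different question: would a new sample be cut in the same place? A continuum with one dominant direction is cut in nearly the same place every time, so it passes.

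At stake is how the primary outcome is read. If the clusters are slices of overall severity, calling them distinct and robust subtypes overstates the result, and every trajectory comparison between them inherits the problem. The planned predictive modelling would not necessarily reveal this, because slices of a severity scale would also be expected to predict later severity or mood outcomes.

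**Working it through.** **The plan's own figure.** Study population states "an estimated 40–80 variables will be included in the statistical model" and "Based on an estimated events per variable (EPV) of 50 to ensure sufficient statistical power". Then 50 × 80 = 4,000 (and 50 × 40 = 2,000), so the target of 4,000 reproduces. It has no bearing on the choice of k. The plan gives no figure for k or for stability, so the check is by definition and by simulation.

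**By definition.**
- Silhouette for a participant is (b − a)/max(a, b), where a is the mean distance to the own cluster and b the mean distance to the nearest other cluster. At k = 1 there is no b.
- The elbow uses the within-cluster sum of squares W(k). W(1) exists (it is the total), but a bend needs a point on either side, so it cannot lie at k = 1.
- Gap(k) = mean log W(k) over reference sets − log W(k). It is defined at k = 1. The first-k rule takes the smallest k with Gap(k) ≥ Gap(k+1) − s(k+1); the alternative takes the global maximum.

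**By simulation.** From the plan: n = 4,000, 60 features (middle of 40 to 80), Z-scores, PCA to 85% of variance, K-means. Assumed: one general severity factor plus five domain factors (loading 0.4); the skewed version is log-normal with general loading 0.6. k ran from 1 to 6, with one data set per scenario, 10 uniform Gap reference sets and 30 bootstrap resamples. ARI is the adjusted Rand index.

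| Scenario | Silhouette picks (value) | Gap, first-k | Gap, maximum | Mean ARI k = 2 | Mean ARI k = 3 |
|---|---|---|---|---|---|
| No clusters, independent | 2 (0.014) | 1 | 1 | 0.05 | 0.05 |
| No clusters, general loading 0.4 | 2 (0.141) | 1 | 3 | 0.98 | 0.93 |
| No clusters, general loading 0.6 | 2 (0.229) | 1 | 1 | 0.96 | 0.93 |
| No clusters, general loading 0.7 | 2 (0.293) | 1 | 6 | 0.95 | 0.97 |
| No clusters, skewed | 2 (0.305) | 5 | 5 | 0.95 | 0.93 |
| Three true clusters | 3 (0.217) | 3 | 3 | 0.88 | 1.00 |

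- *Gap, loading 0.7.* Gap(1) = 1.3991 ≥ 1.3475 − 0.0032 = 1.3443, so the first-k rule stops at 1. The maximum is Gap(6) = 1.4769.
- *Gap, skewed.* Gap(1) = 2.3848 < 2.4632 − 0.0024 = 2.4608, so k = 1 is rejected. The rule stops at k = 5, where 2.5509 ≥ 2.5506 − 0.0026 = 2.5480.
- *Elbow, loading 0.6.* W(k)/W(1) is 1, 0.710, 0.628, 0.595, so successive drops are 0.290, 0.082 and 0.033: a bend at k = 2 without clusters. With independent features the drops are 0.016, 0.011 and 0.008, with no clear bend.
- *Silhouette.* Its size does not settle the matter either: 0.229 and 0.305 in two cluster-free sets exceed the 0.217 from three true clusters.

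**Further runs at the recruited n = 2,937, 60 correlated features, no clusters.**
- With one general and six group factors (four normal and four right-skewed data sets), silhouette was highest at k = 2 in 8 of 8. Mean ARI was 0.93 to 0.96 at k = 2. Gap chose 1 in 4 of 4 normal sets, but 3 or 4 in 4 of 4 skewed ones.
- In a further run, ARI at k = 2 was 0.94 to 0.96. Gap chose 1 (first-k) or 5 (maximum) with normal features, and 3 or 5 with skewed ones.

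Across the correlated cluster-free runs, ARI at k = 2 spans 0.93 to 0.98.

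**Does a null reference discriminate?** In the last run, data with three true clusters exceeded the single-population reference at k = 3: silhouette 0.118 against at most 0.090, and ARI 0.83 against at most 0.78. Cluster-free data did not exceed it on either measure.

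**The case against.** The strongest reply is that the rule already contains an index that can say one cluster. Gap is named beside the other two and chose k = 1 in all the cluster-free normal scenarios tabulated, under the first-k rule. This stands. A reader might infer that the plan can never conclude against subtypes; the document does not support that. The search range, the Gap rule and precedence among the indices are details that a condensed article may leave to the full plan.

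Second, high stability without clusters is conditional. Independent features gave an ARI of 0.05, so it would be wrong to say that stability is high whenever subtypes are absent. The article reports no feature correlations, and its one fully described score, the ISI (mean 15.5, SD 5.8, median 16.0, interquartile range 7.0), shows little skew. This also stands, though Multimodal data integration itself plans for multicollinearity, and Table 1 lists many scales likely to share a severity gradient (ISI, PHQ-9, GAD-7, PSAS, MFI, PHQ-15).

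Third, the simulations are not the full pipeline. Consensus clustering, modality weighting and 1,000 resamples were not reproduced. They illustrate the problem and do not estimate its probability in this study.

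Fourth, the aim is exploratory, and the Background section adds validation at follow-up. A formal test of existence is therefore not owed. That argues against a hard gate on claiming subtypes, but not against a reference for interpreting them.

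What the reply does not remove is the nature of the check. Further detail on the bootstrap, or more iterations, would estimate repeatability more precisely and would still not test for groups.

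**Conclusion.** The point holds in a limited form. Silhouette and elbow cannot select k = 1. Gap can, but in these simulations it failed with skewed features in every run and, when its maximum was used, in two of the four tabulated normal scenarios. The robustness check measures repeatability. If the features share a continuous severity gradient, data without clusters give a mean bootstrap ARI of about 0.93 to 0.98 at k = 2, so a continuum could be presented as robust subtypes. This rests on assumed factor structure and skewness, which are plausible for these scales but not documented. It does not show that the study will report false subtypes, nor that a one-cluster answer is out of reach. It calls for a cheap improvement to the analysis.

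**What to change.** In Subtyping procedures:

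1. Include k = 1 in the search and state which Gap rule is used.
2. Simulate single-population data sets with the observed margins and correlation matrix, for example by a Gaussian copula, and run each through the same scaling, PCA, K-means and resampling steps.
3. Report the observed silhouette and stability at the chosen k against their distribution in those data sets.
4. If the observed values do not exceed that reference, describe the clusters as a partition of a continuum rather than as distinct subtypes.

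No new data or change of design is needed. The costs are some wording, computing time, and the chance of a less favourable conclusion.

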#### Longitudinal modeling

We will use classification and regression methods to investigate whether baseline information can predict follow-up outcomes. Chi-square analysis, repeated measures analysis, and mixed-effects models will be employed to examine the relationships among the cross-sectional data and the changes over time across different visits. For binary outcomes (e.g., the occurrence of anxiety or depression), logistic regression models will be used, while linear regression models will assess continuous outcomes (e.g., changes in the Insomnia Severity Index (ISI) score). Mixed-effects models will analyze longitudinal changes while accounting for individual variability.

Statistical methods may be adjusted as needed based on the actual data, and we will adopt the most appropriate methods for the analyses. Any limitations in the analysis will be thoroughly addressed and elaborated upon in subsequent research publications.

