## Results

In the current study, 127 researchers across study sites received consistent training in clinical interviews, the use of wearable devices, and other psychological assessments. We randomly selected 46 researchers to complete a reliability assessment for 8 clinical structural interviews. The Cochran’s Q values ranged from 29.2 to 43.0, with all p-values > 0.05, indicating a high consistency among interviewers.

From November 28, 2022, to June 30, 2025, approximately 5000 individuals with suspected insomnia disorder were screened. A total of 3134 participants were interviewed, of whom 2937 (93.7%) were recruited and 197 (6.3%) were excluded. Among those recruited, there are 1743 (59.3%) from outpatient clinics and 1194 (40.7%) from community settings. The most common reason for exclusion was psychotic symptoms resulting from other mental disorders, which led to the inability to complete the clinical interview. The recruitment procedure is shown in Fig. 3.

All participants met the ICSD-3 criteria for insomnia disorder, with a mean age of 37.3 ± 12.6 years and 1952 (66.5%) were females. At baseline, 2850 participants (97.1%) were suffering from current insomnia disorder as defined by the clinical interview based on ICSD-3. In terms of comorbidities, assessed by the structured clinical interviews administered via the Zhiyoumian-Researcher app, 505 participants (17.2%) had current depressive disorders, and 613 participants (20.9%) had current anxiety disorders. The mean score of the ISI was 15.5 ± 5.8, with a median (interquartile range) score of 16.0 (7.0). When comparing those from the community setting and clinic, we found that the participants from the clinic are significantly older than their counterparts. But there is no statistical difference in sex, comorbidities, and insomnia severity (Table 2).

**Table 2 Tab2:** Demographics, comorbidities, and insomnia severity in participants from community and clinic settings（*N* = 2937）

	Community(*n* = 1194)	Clinic（*n* = 1743）	*p*
Age, mean±SD	35.9±12.3	38.2±12.3	＜0.001
Gender Female, n(%)	780 (65.3%)	1172 (67.2%)	0.283
Comorbidities, n(%)	364 (30.5%)	484 (27.8%)	0.115
Depressive Disorder	212(17.8%)	293(16.8%)	0.518
Generalized Anxiety Disorder	270(22.6%)	343(19.7%)	0.058
Bipolar Disorder	39(3.3%)	48(2.8%)	0.439
Panic Disorder	15(1.3%)	25(1.4%)	0.748
Post-Traumatic Stress Disorder	25(2.1%)	45(2.6%)	0.460
ISI, mean±SD	15.7±5.84	15.3±5.79	0.101
ISI ≥ 8, n(%)	1104(92.5%)	1602(92.9%)	0.625

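### The follow-up models name individual variability as the only source of dependence and include no site term, so subtype-outcome tests across 33 sites can be too optimistic or confounded by site

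*Protocol article*

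**What the plan says.** The Longitudinal modeling section of the protocol article sets out the follow-up analyses. For binary outcomes such as anxiety or depression, and for continuous outcomes such as change in the ISI, "logistic regression models will be used, while linear regression models will assess continuous outcomes". For repeated visits, "Mixed-effects models will analyze longitudinal changes while accounting for individual variability". The section adds that methods may be adapted to the data.

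Site is not named as a fixed effect, random effect, stratum or cluster in that section. Nor is it named in the sections on descriptive analyses, multimodal data integration or subtyping.

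The cohort is multicentre. Under Study population, "As of June 2025, 33 study sites specializing in psychiatry, neurology, or sleep medicine have taken part in the current study". Study procedures says that each site drew a convenience sample, under recruitment and assessment procedures common to all sites. The only related step at the analysis stage is a sensitivity analysis of community against clinic recruitment, mentioned under Strengths and limitations.

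**The concern.** Trajectories of the subtypes, their risk factors and mental health outcomes are the secondary outcomes, and the Conclusions expect subtypes to predict clinical course. Those claims rest on comparing outcomes between subtypes.

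Several features of the design could make both subtype and outcome depend on site:

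- **Case mix.** Sites differ in specialty and each recruits by convenience, so subtype mix can differ.
- **Care.** Ongoing treatments continue and e-CBTI is optional. Of 2,850 participants with current insomnia, 2,455 received it. Uptake and co-treatment may vary by site.
- **Measurement.** Mental disorders and symptoms are among the clustering features, and anxiety or depression is a named outcome. Diagnoses come from interviews led by site researchers, of whom 127 were trained. A site's rating habits could enter both sides of the comparison.

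If subtype and outcome both cluster by site and site is left out, two things can follow. Standard errors for subtype effects can be too small. If the two sets of site effects are also related, differences between sites appear as a subtype effect.

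**Working it through.** **1. The plan's own figure.** The sample size rests on "an estimated 40–80 variables will be included in the statistical model" and an EPV of 50. At the upper end, 80 × 50 = 4,000, which reproduces the stated total; the lower end gives 40 × 50 = 2,000. The calculation contains no allowance for clustering by site.

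**2. Participants per site.** 4,000 / 33 = 121.2 at target, and 2,937 / 33 = 89.0 on current recruitment. The text can also be read as a principal centre plus 33 collaborating sites. With 34 sites the target figure is 117.6, which changes little.

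**3. Which design effect applies.** Subtype is a characteristic of the individual, not of the site. For such a predictor, with site ignored and unrelated site effects,

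DE = 1 + (m − 1) × ICC(outcome) × ICC(subtype),

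and the actual two-sided error of a nominal 5% test is 2 × [1 − Φ(1.96 / √DE)].

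The article gives no ICC, site sizes or significance level. The ICCs below, equal site sizes and a two-sided 5% level are therefore assumptions.

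| ICC outcome | ICC subtype | DE, m = 121.2 | Error | DE, m = 89.0 | Error |
|---|---|---|---|---|---|
| any | 0 | 1.00 | 5.0% | 1.00 | 5.0% |
| 0.02 | 0.05 | 1.12 | 6.4% | 1.09 | 6.0% |
| 0.02 | 0.10 | 1.24 | 7.8% | 1.18 | 7.1% |
| 0.05 | 0.05 | 1.30 | 8.6% | 1.22 | 7.6% |
| 0.05 | 0.10 | 1.60 | 12.1% | 1.44 | 10.2% |

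Worked example, last row: 1 + 120.2 × 0.05 × 0.10 = 1.60; 1.96 / √1.60 = 1.55; error 12.1%. The effective sample size is 4,000 / 1.60, or about 2,500.

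Unequal site sizes raise these figures. With a coefficient of variation of 0.8, m is replaced by 121.2 × (1 + 0.64) = 198.8. The last row then becomes DE = 1 + 197.8 × 0.005 = 1.99, with an error of about 16%.

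**4. Simulation.** The setting was 33 sites of 121, no true subtype effect, a binary subtype at 50% prevalence and 2,000 runs per setting. Linear regression without site was compared with the within-site (fixed-effect) estimator. Subtype ICC is on the latent scale, so the observed ICC is somewhat lower than in the table above.

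| ICC outcome | Latent ICC subtype | Correlation of site effects | Error, no site | Error, with site | Mean spurious effect, no site (SD) |
|---|---|---|---|---|---|
| 0.02 | 0 | 0 | 5.3% | 5.4% | 0.00 |
| 0.05 | 0 | 0 | 5.1% | 5.0% | 0.00 |
| 0.02 | 0.05 | 0 | 6.9% | 5.6% | 0.00 |
| 0.02 | 0.10 | 0 | 6.1% | 4.3% | 0.00 |
| 0.05 | 0.05 | 0 | 7.6% | 4.8% | 0.00 |
| 0.05 | 0.10 | 0 | 9.1% | 3.8% | 0.00 |
| 0.02 | 0.05 | 0.5 | 14.1% | 4.2% | 0.03 |
| 0.02 | 0.10 | 0.5 | 20.3% | 4.2% | 0.03 |
| 0.05 | 0.05 | 0.5 | 28.4% | 5.8% | 0.04 |
| 0.05 | 0.10 | 0.5 | 43.2% | 4.7% | 0.06 |

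With 2,000 runs the Monte Carlo standard error near 5% is √(0.05 × 0.95 / 2,000), or about 0.5 percentage points. The small reversals between rows are of that order.

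With unrelated site effects the inflation is modest. With correlated site effects confounding dominates. Within-site estimation brings the error back to about 4% to 6% and removes the bias.

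**The case against.** The strongest reply is that this is silence in a condensed article. The text does not say that individual variability is all the models will account for. It leaves methods open to adjustment, and a fuller protocol or analysis plan may specify site. The article also mentions control for sleep medication and a community-clinic sensitivity analysis outside its statistical section, so that section is not a complete list of model terms. This stands as a limit: a reader might infer that the investigators have decided to ignore site, and the document does not show that. It does show that the authors chose to say what the mixed models account for and named only the individual. An open clause on methods does not fix how site enters.

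A second reply is that the harm is conditional. That is correct. A reader might infer that standard errors are certainly too small, or apply the usual cluster design effect 1 + (m − 1) × ICC, which gives 3.4 at an ICC of 0.02 and 7.0 at 0.05. Neither is supported. That formula is for a predictor constant within site, and inflation here needs both subtype and outcome to vary by site. The 0.5 correlation behind the largest errors is an illustration with no figure in the article to support it.

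Third, interviewers shared training, an examination and weekly quality control, and the reported consistency tests were not significant. These steps reduce differences in measurement between sites but do not equalise case mix or care. The similar ISI and comorbidity by community and clinic in Table 2 concern setting, not site.

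Fourth, stable additive site differences in level cancel in ISI change, and attrition lowers the number per site and so the inflation. Both hold, but site differences in the change itself remain.

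**Conclusion.** The point holds in conditional form. The follow-up models as stated name one source of dependence, the individual, and carry no site term, in a cohort from 33 sites that differ in specialty and each recruit by convenience. Run that way, subtype-outcome tests can be anti-conservative and can absorb differences between sites.

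With assumed ICCs of 0.05 to 0.10 for subtype and 0.02 to 0.05 for outcome, about 121 participants in each equal-sized site and unrelated site effects, the actual error of a nominal 5% test is about 6% to 12%. It is near 5% if subtype mix does not differ by site. It is higher if site sizes are very unequal or if site effects on subtype and outcome are correlated. Because the article reports no ICC, the size for this trial cannot be fixed. The point concerns the secondary, longitudinal comparisons.

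**What to change.** State how site enters the follow-up models:

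- **Mixed models:** add a random intercept for site above the participant level.
- **Logistic and linear models:** include site as a fixed effect, or as a random intercept with cluster-robust standard errors.
- **Where confounding by site is the concern:** use fixed or within-site effects, because a random intercept alone still draws on comparisons between sites.
- **Reporting:** tabulate subtypes by site, so that readers can see whether subtype mix differs.

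Resampling whole sites for bootstrap intervals is optional.

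The cost is low. The change is one term in each model, it uses the participant's recruiting site, and intervals become slightly wider. Only the within-site linear estimator was checked by simulation here. The random-intercept, logistic and bootstrap versions are standard choices but were not tested.
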